### Analysis

R V.3.6.3 (R Foundation for Statistical Computing, Vienna, Austria) or higher will be used for data analysis. The significance level of all tests will be set at <0.05. For the majority of data, descriptive statistics will be used, but correlation tests will also be performed for the secondary objectives of this study.

When the level of agreement to a proposition is measured, 1–4 Likert scale results will be treated as ordinal variables. When frequencies are measured, they will be treated as categorical variables. The data will be assessed for normal distribution. Depending on the type of distribution found, random or fixed models will be used to investigate correlation between answers.

Normally distributed data will be analysed using the Student’s t-test. Data will be represented as means with their SD (±SD). Not normally distributed continuous data will be analysed using the non-parametric Mann-Whitney U test. Outcomes will be presented as medians and their IQRs. Normality of continuous variables will be assessed with the Shapiro-Wilk test and graphically in histograms. Homogeneity of variances will be tested using the Levene’s test. Categorical data will be analysed using the χ^2^ test.

Correlation tests will be performed to analyse associations between baseline characteristics, cultural capital, music listening type, dyspnoea severity and specific expectations-propositions. Depending on the type of variable (continuous or categorical), either t-tests, logistic or linear regression analysis, respectively will be used.

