### Setting and participants

In the Netherlands, pulmonary rehabilitation is provided either by general hospitals, university hospitals or by specialised rehabilitation clinics. Outpatient secondary care programmes, typically provided by general hospitals, are most common. These programmes require patients to travel to the hospital or clinics several times a week to participate in exercise sessions under the supervision of specialised exercise therapists or physiotherapists. Additionally, patients attend consultations with other members of the multidisciplinary team such as psychologists or social workers. In the meantime, exercises for home training are usually provided. However, when the patient is in such condition that outpatient rehabilitation is not preferable or possible, tertiary care pulmonary rehabilitation will be offered. Provided only by the dedicated rehabilitation clinics, patients are admitted for multiple weeks (usually 8–12 weeks) to complete the rehabilitation programme. On completion of a programme, patients are referred to dedicated physiotherapists to maintain physical fitness as long as possible.

The study population comprises both patients and healthcare professionals involved in pulmonary rehabilitation. Patient inclusion criteria are as follows: (1) enrolment in a pulmonary rehabilitation programme, either inpatient or outpatient, at secondary or tertiary care level and (2) sufficient understanding of the Dutch language. Exclusion criteria for the study are (1) insufficient understanding of the Dutch language, (2) significant hearing impairment and (3) people who refuse to listen to music due to religious objections.

Healthcare professionals are eligible if they hold a medical or paramedical position at one of the study sites and are actively engaged in pulmonary rehabilitation programmes. Relevant roles include physicians, nurses, physiotherapists, exercise therapists, occupational therapists, speech therapists, psychologists, social workers and dietitians. No exclusion criteria apply for healthcare professionals.

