### Data collection and recruitment

Data collection will be conducted over a period of two predetermined weeks at each study site. During this period, members of the research team will visit the different study sites and approach potential participants in person, inviting them for participation. Recruitment will primarily occur after group exercise sessions or during ward visits for patients admitted to rehabilitation clinics. Specific recruitment times will be coordinated in close collaboration with each site. Patients who consent to participate may choose to complete the questionnaire either online or in paper format.

Healthcare personnel will be recruited primarily via email. Email lists will be compiled in cooperation with the participating institutions to identify all staff involved in the pulmonary rehabilitation programmes. Where possible, healthcare workers too will be recruited in person and will be provided with the choice to either fill out the questionnaire online or on paper. In both groups, the online surveys will be available using Microsoft forms, and the data capture programme used is Castor.

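### Random versus fixed models are chosen by the data's distribution, which is the wrong criterion, and no grouping factor is named; unadjusted tests can be anticonservative for characteristics that vary mainly between sites

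*Protocol article*

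**What the plan says.** All of the statistical plan is in the Analysis section of the protocol article.

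- It starts from a normality check, "The data will be assessed for normal distribution", and goes straight on to: "Depending on the type of distribution found, random or fixed models will be used to investigate correlation between answers". It does not say which distribution leads to which model, or what the random or fixed effect would be attached to (site, respondent or questionnaire item).
- The other methods are "Normally distributed data will be analysed using the Student’s t-test", "Not normally distributed continuous data will be analysed using the non-parametric Mann-Whitney U test" and "Categorical data will be analysed using the χ^2^ test". Associations with baseline characteristics, cultural capital, listening type and dyspnoea are to use t-tests or logistic or linear regression. None is given a site term, stratification or clustered variance.
- On the error level: "The significance level of all tests will be set at <0.05".
- The 1–4 agreement items are to be handled as ordinal.

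The sampling is multi-site. Under Data collection and recruitment: "Data collection will be conducted over a period of two predetermined weeks at each study site", with patients approached mainly after group exercise sessions or on wards. Under Setting and participants: "pulmonary rehabilitation is provided either by general hospitals, university hospitals or by specialised rehabilitation clinics", and inpatient tertiary programmes run only at dedicated clinics. The number of sites, the expected number of respondents and any ICC are not stated.

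**The concern.** Two decisions are merged in one sentence. The distribution or measurement level of an outcome bears on the model family or on a rank-based alternative, for example an ordinal model for a four-category item. Whether an effect is random or fixed depends on the grouping of the observations and on whether inference is to these groups or to a wider population of them. A normality result says nothing about that, so the sentence fixes a wrong rule and, with no grouping factor, cannot be carried out as written.

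The grouping matters because patients at one site share a programme, staff and local habits, and their expectations of music may be correlated. The other named tests treat respondents as independent. For a characteristic that differs mainly between sites, such as inpatient versus outpatient setting or care level, this can make the standard error too small and the 5% level nominal only. The secondary objectives (associations with expectations, and patients versus professionals) are where tests are used.

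**Working it through.** **No figure to reproduce.** The Sample size section gives response-rate targets only (40% of patients, 60% of professionals). Respondents per site (m), number of sites and ICC below are all assumptions, shown as ranges.

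**Case 1: characteristic constant within a site.** Design effect DE = 1 + (m − 1) × ICC. True two-sided type I error of a nominal 5% test = 2 × [1 − Φ(1.96/√DE)].

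| m | ICC | DE | True type I error |
|---|---|---|---|
| 15 | 0.02 | 1 + 14 × 0.02 = 1.28 | 8% |
| 15 | 0.05 | 1 + 14 × 0.05 = 1.70 | 13% |
| 15 | 0.10 | 1 + 14 × 0.10 = 2.40 | 21% |
| 30 | 0.02 | 1 + 29 × 0.02 = 1.58 | 12% |
| 30 | 0.05 | 1 + 29 × 0.05 = 2.45 | 21% |
| 30 | 0.10 | 1 + 29 × 0.10 = 3.90 | 32% |

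**Case 2: contrast balanced within every site.** True SE / naive SE = √(1 − ICC). For ICC 0.01, 0.05 and 0.10 this is 0.995, 0.975 and 0.949, so the naive SE is slightly too large. Putting 1.96/√(1 − ICC) into the same normal formula gives true errors of about 4.9%, 4.4% and 3.9%.

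**Simulation check.** Null surveys with 10 sites × 20 respondents, normal responses with a site effect, unadjusted Student's t-test at 5%, 10,000 replicates per cell:

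| Type of characteristic | ICC 0.01 | ICC 0.05 | ICC 0.10 |
|---|---|---|---|
| Constant within site | 7.4% | 16.0% | 25.5% |
| Respondent-level, prevalence 30% to 70% across sites | 5.7% | 5.8% | 6.1% |
| Balanced within each site | 5.0% | 4.4% | 3.9% |

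For m = 20 the Case 1 formula gives 7.2%, 16.0% and 25.0%, in line with the first row. The third row agrees with Case 2.

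**Which case applies to the plan?** Under Study parameters and tools, the baseline items named are age, gender, educational level, and medication use or professional role. These vary between respondents, so the second row is the closest. Professionals work at the study sites, so the patient–professional contrast lies largely within sites and is nearest the third row. Setting and care level appear in the eligibility criteria but are not named as covariates. The first row applies if they, or something else that varies mainly by site, are tested.

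**The case against.** The strongest reply has three parts.

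1. *The article is silent on site; it does not say that site will be ignored.* An article may leave site adjustment to a fuller document, and the sentence may be a garbled reference to it. This stands as far as it goes: silence is not a decision to ignore clustering. A reader might also infer that site adjustment would be switched on or off by a Shapiro-Wilk result. The sentence speaks of correlation between answers and does not mention site, so that is an inference. But the sentence does state a selection rule, and the rule is wrong. If it means items within a respondent, the grouping factor changes and the criterion is still wrong.

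2. *The large error rates concern analyses that the article does not name.* This largely stands. A reader might infer that standard errors will be too small throughout and that the 5% level fails generally. The check does not support that: the error is slight for respondent-level characteristics and can reverse for a within-site contrast. A reader might also infer that intervals for pooled descriptive results will undercover. The Analysis section plans SDs and IQRs and mentions no confidence intervals.

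3. *The survey is exploratory.* This also stands. The primary objective is descriptive and tests serve only the secondary objectives, which limits the severity but does not make the sentence usable.

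**Conclusion.** The point holds in a limited form and is of moderate severity. What is certain from the text is that the criterion for random versus fixed models is wrong and that no grouping factor is named.

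What is conditional is the statistical consequence. Unadjusted tests could have a type I error of 8% to 32% for characteristics constant within a site, for an assumed 15 to 30 respondents per site and ICC of 0.02 to 0.10. For respondent-level characteristics unevenly spread over sites, it is about 6% in the simulated setting. For patients versus professionals the unadjusted test may be slightly conservative, at 4% to 5% if the contrast is balanced within sites. The documents do not support a general claim that standard errors will be too small.

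**What to change.** Replace the sentence with wording such as:

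> The outcome type determines the model family (for example, an ordinal model for the 1–4 items). Association and group-comparison analyses are done in regression models that account for study site (random intercept, or fixed site effects if there are few sites), irrespective of the distribution of responses.

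Then:

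- Use these models for inference in place of the unadjusted t, Mann-Whitney and chi-square tests.
- Include setting (inpatient or outpatient) as a covariate only where it is not aliased with site. Where each site offers one setting, fixed site effects absorb it and its effect cannot be estimated.
- If confidence intervals for pooled results are reported, use site-clustered variance.
- Make sure that a site code is carried on the online link or paper batch. The Ethics and dissemination section says that answers cannot be traced once returned, so a missing code could not be added later. Site combined with professional role could single out a lone staff member, so collapse or suppress small role-by-site cells, including in shared raw data.

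The cost is a change of wording, a site code, some anonymity handling, and somewhat wider intervals for characteristics that vary between sites.

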### Secondary objectives

To identify associations between baseline characteristics of patients and their expectations of the effect of music interventions on breathlessness or exercise tolerance.To identify differences in expectations regarding music interventions among patients and their healthcare workers.

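### Student's t-test is the only parametric two-group test named and Levene's test leads nowhere, so the 0.05 level is not assured where subgroup sizes and spreads differ; Welch's test as default is a free improvement

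*Protocol article*

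**What the plan says.** Everything relevant is in the Analysis section of the protocol article.

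- Level: "The significance level of all tests will be set at <0.05". Sidedness is not stated; two-sided is assumed here.
- Parametric route: "Normally distributed data will be analysed using the Student’s t-test".
- Non-parametric route: "Not normally distributed continuous data will be analysed using the non-parametric Mann-Whitney U test".
- Choice between the two: "Normality of continuous variables will be assessed with the Shapiro-Wilk test and graphically in histograms".
- Variance check: "Homogeneity of variances will be tested using the Levene’s test". The section does not say what happens if this test is significant, and no unequal-variance test is named anywhere in the article.
- Expectation items: "When the level of agreement to a proposition is measured, 1–4 Likert scale results will be treated as ordinal variables".
- Associations with baseline characteristics: "Depending on the type of variable (continuous or categorical), either t-tests, logistic or linear regression analysis, respectively will be used".

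The Sample size section gives target response rates (40% of patients, 60% of professionals) and no power analysis. No expected group sizes or SDs are given.

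**The concern.** Student's t-test pools the two variances. If the groups are of equal size, or the variances are equal, that does little harm. If both differ, the pooled standard error is wrong. It is too small when the smaller group is the more variable one, so the test rejects too often. It is too large in the opposite case, so the test rejects too rarely.

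Subgroups in this survey are observed, not allocated, and nothing in the design balances them, so unequal sizes are likely. Levene's test is evidently meant as the safeguard, but as written it changes nothing. Even if it were given a consequence, choosing between tests by a variance pre-test is weakest in small samples, where the pre-test has little power.

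At stake is whether a few associations in the first secondary objective, mainly those involving age, are declared or missed because of a difference in spread and not in level.

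**Working it through.** **Inputs from the article:** level 0.05; Student's t for normal data; Mann-Whitney U otherwise; Shapiro-Wilk and Levene as checks.

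**Assumed inputs:** group sizes, SD ratios, normal data, no true mean difference, two-sided testing.

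**Step 1. The stated level under its own assumption.** With equal SDs Student's test has an exact level of 0.05. Simulation with 20,000 replicates gave 0.047 to 0.051 over sizes from 30/10 to 200/50. The stated figure reproduces.

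**Step 2. Unequal sizes and SDs, by formula.** The large-sample level is

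level = 2 × [1 − Φ(1.96 × SE_pooled / SE_true)]

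*Groups 160 and 40, smaller group with 1.3 times the SD:*
- pooled variance = (159 × 1 + 39 × 1.69) / 198 = 224.91 / 198 = 1.136
- SE_pooled² = 1.136 × (1/160 + 1/40) = 1.136 × 0.03125 = 0.0355
- SE_true² = 1/160 + 1.69/40 = 0.0485
- SE ratio = √(0.0355 / 0.0485) = 0.856
- level = 2 × [1 − Φ(1.677)] = 9.4%

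*Same sizes, larger group with 1.3 times the SD:*
- pooled variance = (159 × 1.69 + 39 × 1) / 198 = 307.71 / 198 = 1.554
- SE_pooled² = 1.554 × 0.03125 = 0.0486
- SE_true² = 1.69/160 + 1/40 = 0.0356
- SE ratio = 1.169
- level = 2 × [1 − Φ(2.29)] = 2.2%

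**Step 3. The same case by simulation, with the possible routes.** Where runs were repeated, the range is shown.

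| Route (160/40, SD ratio 1.3) | Smaller group more spread | Larger group more spread |
|---|---|---|
| Shapiro-Wilk, then Student or Mann-Whitney; Levene not acted on | 9.2–9.3% | 2.3–2.6% |
| Welch only after a significant Levene test | 6.4–6.9% | 4.1–4.6% |
| Welch always | 4.7–4.9% | 4.9–5.5% |

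At an SD ratio of 1.1 Student's test gives only 6.6% and 3.9%. With equal SDs all routes are near 5%.

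**Step 4. Range over other assumptions, smaller group more spread.** Each cell gives SD ratio 1.5, then 2.

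| Sizes | Student | Levene, then Welch | Welch always |
|---|---|---|---|
| 50/50 | 0.053, 0.049 | 0.053, 0.048 | 0.053, 0.048 |
| 60/30 | 0.083, 0.114 | 0.058, 0.054 | 0.049, 0.053 |
| 120/40 | 0.105, 0.154 | 0.055, 0.051 | 0.049, 0.051 |
| 200/50 | 0.121, 0.180 | 0.057, 0.051 | 0.052, 0.051 |
| 30/10 | 0.109, 0.153 | 0.090, 0.088 | 0.051, 0.052 |

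With the larger group more spread, Student's level at the unequal sizes falls to 0.011–0.026 (ratio 1.5) and 0.005–0.017 (ratio 2).

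At 30/10 with the smaller group more spread, Levene's test is significant in only 25% (ratio 1.5) or 60% (ratio 2) of samples, which is why it protects poorly there. If a significant Levene test led instead to Mann-Whitney U, the only other two-group test named for continuous data, the level with this pattern would be 0.064 to 0.115 over the unequal sizes tried.

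**Step 5. Which variables reach this route.** The 1–4 propositions are declared ordinal. The Borg ratings are discrete 12-point scores. Borg-like data simulated with an assumed mean of 4 and SD of 1.5 to 2.5 failed Shapiro-Wilk in 100% of samples of 160, so they would probably go to Mann-Whitney U. The two 1–7 cultural-capital items fall outside the stated ordinal rule, and their route is not given. That leaves mainly age and any other roughly normal continuous variable.

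**The case against.** The strongest reply is that the article never says data failing Levene's test still go to Student's test. Running a variance check and ignoring it is the least plausible reading, and a condensed article may leave the next step to a fuller document. This stands. A reader might infer that the plan commits to Student's test regardless, and that 9% is the error rate of the plan as written. The text does not support that; 9% is what Student's test does if nothing follows from Levene. On the natural reading, a switch to Welch, the level is 0.044 to 0.058 at 60/30 and above for SD ratios of 1.5 and 2. It is clearly off only in small groups and modestly off at the milder ratio of 1.3.

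A reader might also infer that the second secondary objective, "To identify differences in expectations regarding music interventions among patients and their healthcare workers", is affected. It concerns ordinal items, and the professionals' questionnaire omits dyspnoea severity, so the Borg ratings cannot be compared between those groups. Nor does the article split any proposition into agree versus disagree, so a two-group comparison of age for each of the 27 propositions is not something it plans. Regression is also listed for the associations.

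Finally, group sizes and SDs are assumed throughout, and checking assumptions before a t-test is conventional. Histograms will be used alongside Shapiro-Wilk, which the simulation did not model. All of this limits the reach. It does not remove the point that the article itself names the equal-variance test and a check that leads nowhere, when a better default exists at no cost.

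**Conclusion.** The point holds as a minor, free improvement. The 0.05 level is not assured for roughly normal continuous variables, mainly age, compared between observed patient subgroups that differ in both size and spread. Under the illustrative 160/40 split with an SD ratio of 1.3, the level is about 9% or 2.5% for Student's test, about 6.5% or 4.5% for Welch after a significant Levene test, and about 5% for Welch throughout. These figures rest on normal data and on sizes and SDs that the article does not give. With equal groups or equal SDs the problem disappears.

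It would be too strong to say that the survey's tests are known to miss their level: unequal group sizes are a reasonable inference, but nothing in the article indicates how far spreads differ. The comparisons concerned are secondary and exploratory in a study that is mainly descriptive, so the feasibility conclusions do not depend on this.

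**What to change.** In the Analysis section:

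- Name Welch's t-test as the default for two-group comparisons of continuous variables, reported as the mean difference with a 95% CI.
- Drop Levene's test as a selector.
- Assign the ordinal measures (1–4 propositions, Borg ratings, 1–7 items) in advance to rank-based or ordinal-model analyses.
- Keep histograms for description. Shapiro-Wilk then has nothing left to select.

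The cost is one or two sentences before the data are seen. There is no meaningful penalty when variances are equal: with equal SDs both tests reject at close to 5% in the simulations (for example 0.050 for Student and 0.052 for Welch at 120/40).

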### Burden and risk

No significant burden is associated with this research. The questionnaire will take 10–15 min for patients to complete and 5–10 min for healthcare workers. Usual care will not be altered when participating in this study.

### Potential limitations, strengths and future use

This study has a few potential limitations to take into account. The most important limitation of the study is the fact that for the main construct of interest, a new questionnaire had to be developed which was not previously validated. Consequently, certain reliability parameters remain unknown until completion of data collection, as the instrument will be tested in the context of this study for the first time. Internal consistency will be assessed post hoc using Cronbach’s alpha. Nevertheless, efforts have been made to maximise content validity of the questionnaire by putting it through several rounds of review with professional experts as well as with experts by experience. Therefore, the research team believes the questionnaire to sufficiently assess the different constructs of interest.

Another limitation concerns the measurements of the operationalised factors such as cultural capital and music listening style. For feasibility reasons, not the complete validated instruments are implemented in the survey. Instead, only those parts that are considered most relevant to our survey are used resulting in the fact that outcomes of these parameters should be merely interpreted as indicative, and not as a valid representative measurement of the intended constructs. Correlation analysis shall therefore be interpreted with care when performed with these constructs.

A final limitation of this study is its potential selection bias. Although the study will not be presented as a study into ‘music interventions’, but a study into expectations of ‘non-pharmacological interventions’, a risk of selection bias will nevertheless exist with this framing method. By recruiting patients in person, the research team aims to mitigate this risk of bias since the framing will be done in a standardised way by the research team itself ensuring consistent communication across sites.

In contrast, this study also knows several strengths. To our knowledge, it is the first investigation into expectations of music interventions among patients undergoing pulmonary rehabilitation. The findings will provide valuable information regarding the feasibility of implementation and the goals for which future music interventions could best be designed. It might provide insight into patient subgroups with the highest expectations from music interventions, who consequently could possibly benefit most due to an increased placebo effect.

In the introduction of this paper, two methodological challenges in music intervention studies are introduced: the selection bias and the placebo effect. In the future, the questionnaire developed for this study could be valuable in addressing both of these problems. If the questionnaire after this validation study finally will be employed as a baseline measurement for future music intervention studies, it will enable comparisons between included patients and the general population of pulmonary rehabilitation patients, providing insight into the selection bias that might have occurred during the recruitment of patients. Possibly, expectations on music interventions of participants included in new randomised trials are higher than those of the general population, thus confounding outcomes. By incorporating this questionnaire as a baseline assessment, researchers can quantify the extent of selection bias.

Furthermore, because patient expectations will be measured on an ordinal scale in this survey, future analysis could be corrected for patients’ baseline expectations. This might provide valuable information on how treatment expectations influence outcomes, possible discriminating between placebo and an inherent treatment effect. Thus, not only the selection bias, but also the possible placebo effect could be reviewed in a quantitative way when this questionnaire is used in future research. Since selection bias and placebo by expectation are common limitations of many (music intervention-) studies, we advocate measurements of treatment expectations before every music intervention study using the questionnaire developed for this study after completion of its validation process.

